A PILOT STUDY OF CONCURRENT CAPECITABINE ( XELODA ) AND EXTERNAL BEAM RADIOTHERAPY FOR OSSEOUS METASTASES FROM BREAST CANCER.

BACKGROUND

Much of the clinical practice of oncology involves palliative care. In this setting ,the emphasis is on alleviation of symptoms and preservation or improvement of quality of life. A large body of clinical evidence documents the effectiveness of local-field external beam radiotherapy in palliation of pain from osseous metastases (1). Despite this general agreement, controversy remains regarding the optimal dose and fractionation schedule. Prospective phase III clinical trials (2-6), today, have failed to demonstrate superiority of one schedule over another ,and as a result, the patterns of practice of remain diverse in duration and intensity.

Between 1974 and 1980 the RTOG conducted a large national study to determine the effectiveness of five different dose fractionation schedules(2). A total of 1016 patients were entered ,266 into a “solitary metastasis” stratum, and 750 into a ”multiple metastasis “ stratum. The former were randomly assigned to treatment with 40,5Gy in 15 fractions or 20Gy in 5 fractions. The latter were assigned to 30Gy in 10 fractions, 15 Gy in5 fractions ,20 Gy in 5 fractions, or 25 Gy in 5 fractions. A quantitative measure of pain ,based on severity and frequency of pain, and the type and frequency of pain medications used, was devised to evaluate response. Overall, 89% of patients experienced minimal relief. There were no significant difference between the treatment arms in both strata. The initial pain score was found to be a useful predictor ; patients with high score were less likely to respond and were less likely to experience a complete response. Patients with breast and prostate cancer were significantly more likely to respond than patients with lung or other primary lesions. Patients completing their treatment as planned had significantly higher rates of complete response than those who did not .While some relief was experienced almost invariably within the first four weeks, complete relief was first reported later than four weeks after start of treatment in about 50 % of patients .The median duration of minimal and complete pain relief was 20 and 12 weeks ,respectively. There were no significant differences in duration of pain relief between the different arms It was concluded that all treatment dose schedules were equally effective.

A reanalysis of the RTOG study was reported by Blitzer (7).Using a stepwise logistic regression, he examined the effect of the number of fractions, the dose per fraction, and solitary versus multiple metastases, on the probability of attaining complete pain relief and the need for retreatment. This multivariate technique allowed patients with solitary and multiple metastases to be analyzed together. By increasing the number of subjects and events the statistical power of the analysis was outcome. There was no correlation of the time dose factor with outcome (8). It was concluded that the more protracted schedules resulted in improved pain relief.

Price et al. randomized 288 patients to receive either 8 Gy in one fraction or 30 Gy in 10 daily fractions. Pain was assessed using a questionnaire completed by the patients at the home on a daily basis. No differences were found in the probability of attaining pain relief, the speed of onset or the duration of relief between the two arms(4). Hoskin et al. randomized 270 patients to receive either 4 Gy or 8 Gy in one fraction (3) Pain assessed by the patient) and analgesic usage were recorded before treatment and at 2,4,8 and 12 weeks. At 4 weeks the response rates were 69% for 8 Gy and 44% for 4 Gy (p<0.001). The duration of the effect was independent of dose.

Two other randomized trials have been reported (5,6). Given the small difference in the Biological Effective Dose ( BED) between the arms (6) and the small number of patients accrued (5,6), it is not surprising that no differences between the treatment arms were detected.

RTOG have reported the results of a pooled data dose‑response analysis (11). A computerized literature search was conducted to identify prospectively randomized clinical studies which addressed this issue and the results of these studies (2‑6) were pooled together to form a database for analysis. The endpoint selected for analysis was complete response (CR). It was felt that this endpoint was most likely to be evaluated in a consistent fashion by different investigators. One study (6) was excluded from the analysis because outcome was not reported using conventional definitions of complete and partial response. To allow comparison of the different study arms, the BED was calculated for each schedule. Odds ratios calculated for various dose levels showed a statistically significant increase from 1.00 to 3.32 as the BED increased from 14.4 Gy to 5 1.4 Gy.

For the first time, RTOG analysis demonstrated a highly significant dose‑response relationship for palliation of pain from bone metastases with radiotherapy. Furthermore, there was no evidence of flattening of the dose­-response curve within the dose range tested, suggesting that further gains can be realized at doses outside of the range tested. We propose a phase II clinical trial in which the biological effective dose will be increased by the concurrent use of a radiosensitizer. The main advantage of this approach over escalation of the physical dose is the avoidance of increase in the overall treatment time.

Capecitabine is a fluoropyrimidine carbamate with antineoplastic activity. It is an orally administered systemic prodrug of 5'‑deoxy‑5‑fluorouridine (5'‑DFUR) which is converted to 5‑ Capecitabine is readily absorbed from the gastrointestinal tract. In the liver, a 60 kDa carboxyesterase hydrolyzes much of the compound to 5'‑deoxy‑5‑fluorocytidine (5'‑DFCR). Cytidine deaminase, an enzyme found in most tissues, including tumors, subsequently converts 5'‑DFCR to 5'‑deoxy‑5‑fluorouridine (5'‑DFUR).. The enzyme, thymidine phosphorylase (dThdPase), then hydrolyzes 5'‑DFUR to the active drug 5‑FU. Many tissues throughout the body express thymidine phosphorylase. Some human carcinomas express this enzyme in higher concentrations than surrounding normal tissues. Both normal and tumor cells metabolize 5‑FU to 5­fluoro‑2‑deoxyuridine monophosphate (FdUMP) and 5‑fluorouridine triphosphate (FUTP). These metabolites cause cell injury by two different mechanisms. First, HUMP and the folate cofactor, N5‑10­methylenetetrahydrofolate, bind to thymidylate synthase (TS) to form a covalently bound ternary complex. This binding inhibits the formation of thymidylate from uracil. Thymidylate is the necessary precursor of thymidine triphosphate, which is essential for the synthesis of DNA, so that a deficiency of this compound can inhibit cell division. Second, nuclear transcriptional enzymes can mistakenly incorporate FUTP in place of uridine triphosphate (UTP) during the synthesis of RNA. This metabolic error can interfere with RNA processing and protein synthesis. Capecitabine is already approved for use in patients with metastatic breast cancer resistant to both paclitaxel and an anthracycline‑containing chemotherapy regimen.

Although 5FU is an established radiosensitizer, the exact mechanism by which it enhances cell kill is not well understood. Sensitization is schedule dependent and is maximal when a cytocidal concentration of 5FU is given after the radiation exposure (12). The effect does not result from increased sublethal damage or inhibition of sublethal damage repair (12,13). Current evidence suggests that radiosensitization by 5FU is mediated through its effects on DNA rather then RNA (14). In vivo (15) as well as clinical studies (16) have demonstrated the superiority of continuous over bolus infusion of 5FU.

Over the last several decades, concurrent 5FU and radiation have been used successfully in a variety of malignancies. Several important lessons have been learned from clinical trials (16). Simultaneous delivery of large (IV bolus) doses of 5‑fluorouracil with irradiation is associated with improved survival compared to treatment with radiation alone, but at a price of increased normal tissue toxicity. These side effects can be ameliorated by using protracted venous infusion. This is an efficacious approach, with a wide therapeutic index, which permits concurrent treatment of micrometastatic disease and radiation sensitization.

Combined‑modality therapy, including irradiation and concurrently administered 5FU based chemotherapy, has become the mainstay of therapy for anal and rectal cancers. Protracted venous infusion chemoradiation is also used in the preoperative management of rectal cancer and in the nonoperative management of anal cancers. The Gastrointestinal Tumor Study Group (GITSG) has demonstrated a significant survival advantage for patients who receive adjuvant combined radiation and bolus 5FU following curative resection of pancreatic cancer (17,18). Similar advantages have been demonstrated in unresectable pancreatic cancers. Significant advantages have also been shown for concurrent chemotherapy regiments containing 5FU in esophageal cancer (19), squamous cell carcinoma of the Head and Neck (20,21), and carcinoma of thecervix (22).

There is very limited experience with the use of capecitabine and radiation. Based on its relative selectivity and the increase in tumor cell 5FU levels, it should be expected that capecitabine will provide superior radiosensitization at equivalent or reduced systemictoxicity levels**.** Interestingly, it has been recently reported that radiation induces thymidine phosphorylase and enhances the efficacy of capecitabine in human cancer xenografts (23). This may further enhance the synergistic effects, and consequently the therapeutic ratio.

In RTOG study a substantial number of patients with gastrointestinal malignancies treated with concurrent radiotherapy and capecitabine at a dose of 1600 mg/m2/day (5 days a week) with very little toxicity(24 ).In phase II study of chemoradiation for rectal cancer 1650mg/m2/d of capecitabine for 14 days was safe and well-tolerated treatment(25).

In this study we will investigate the feasibility of concurrent Capecitabine and external beam radiotherapy, as well as collect preliminary data regarding the efficacy of this regimen.

**OBJECTIVES**

Hypothesis: Given the hypothesis that regimens employing greater intensity radiation yield higher rates of pain relief, radiosensitization using a tumor targeted drug like Xeloda should improve the rate of complete pain relief as compared to radiosensitization with 5FU alone.

Primary Objective:

To determine the frequency and duration of pain relief and narcotic relief for the proposed regimen.

Secondary Objective:

To determine the toxicity of concurrent Capecitabine and radiotherapy in breast cancer patients with bone metastases.

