**Eligibility Criteria**

Patients with metastatic breast will be allowed on the study regardless of their prior exposure to chemotherapy. Today, there is no evidence to suggest crossresistance between radiotherapy and prior chemotherapy, or that response to radiotherapy is related in any way to the number of lines of chemotherapy used in a particular patient. Good palliative responses can often be achieved in heavily pretreated patients.

1.The patient must be 18 years of age or older.

2.The patient must have histologically proven breast adenocarcinoma.

3. Radiographic evidence of bone metastasis is required .Acceptable studies include plain radiographs, radionuclide bone scans, computed tomography scans and magnetic resonance imaging.

4 .The patient must have pain that appears to be related to the radiographically documented metastasis.

5. Patients receiving systemic therapy with Capecitabine to metastatic disease (according to health basket ).

6. Patients must have an estimated life expectancy of 3 months or greater.

7. Patients will be eligible for treatment of multiple metastases only if these can be included in no more than two treatment sites.

8. Signed study‑specific informed consent.

9 Karnofsky Performance Status > 40.

10**.** Calculated Creatinine Clearance > 50 ml/min

11.ALT and AST no greater than 3‑5 times the institutional normal; bilirubin and serum creatinine no greater than 1.5 times normal; ANC greater than 1500, and platelets at least 100,00.

Exclusion Criteria

1. Prior radiation therapy or prior palliative surgery to the painful site.

2. Impending fracture of the treatment site or planned surgical fixation of the bone.

3. Patients with clinical or radiographic evidence of spinal cord or cauda equina compression.

4. Patients receiving systemic radionuclides (strontium, samarium, etc.) within 60 days prior to registration.

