**Radiation Dose**

All patients will receive radiotherapy to a dose 30 Gy in 10fractions (3 Gy per fraction) over two weeks.

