**CHEMOTHERAPY**

Chemotherapy with capecitabine tablets will be given concurrently with radiotherapy in the dose 1400 mg/m2 orally, in two daily divided doses.

Total daily dose rounded to the nearest 500 mg and divided into morning and evening

Doses, as per the following table:

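### The only stated hypothesis claims more complete pain relief than 5FU radiosensitization, but one uncontrolled capecitabine regimen with no 5FU reference rate can neither support nor refute it

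*Protocol*

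**What the plan says.** Protocol, OBJECTIVES, gives a single hypothesis, and it is comparative: capecitabine radiosensitization "should improve the rate of complete pain relief as compared to radiosensitization with 5FU alone". The two objectives that follow it have no comparator. The primary one is "To determine the frequency and duration of pain relief and narcotic relief for the proposed regimen", and the secondary one is "To determine the toxicity of concurrent Capecitabine and radiotherapy in breast cancer patients with bone metastases". The end of BACKGROUND announces a feasibility study that will "as well as collect preliminary data regarding the efficacy of this regimen", and the title calls the study a pilot.

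Treatment is uniform. Under Radiation Dose, "All patients will receive radiotherapy to a dose 30 Gy in 10fractions". Under CHEMOTHERAPY, "Chemotherapy with capecitabine tablets will be given concurrently with radiotherapy". No allocation, control group or historical reference is described.

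Eligibility Criteria, item 5, lists "Patients receiving systemic therapy with Capecitabine to metastatic disease". PRETREATMENT EVALUATION does not ask when capecitabine was started.

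**The concern.** A hypothesis tells the reader what the data are meant to decide. This one names a comparator, 5FU with radiotherapy, that appears neither in the design nor as a reference figure. Whatever response rate is observed, the hypothesis stays where it was.

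The second difficulty is attribution. BACKGROUND itself says that capecitabine is approved for metastatic breast cancer resistant to certain earlier regimens, so it may relieve bone pain by acting on the disease. Patients enrolled under item 5 receive it as systemic treatment as well as alongside radiotherapy.

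At stake is the conclusion. A high complete response rate set beside this hypothesis invites a claim that sensitization works, or works better than 5FU, when radiotherapy or systemic treatment alone might have produced it.

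**Working it through.** The protocol states no figure to reproduce for this comparison, so the check is mainly a comparison of sections.

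**1. Is there a 5FU reference?**
- Design: Radiation Dose and CHEMOTHERAPY describe one regimen for everyone. The words single arm do not appear, but no other reading fits.
- Literature: the 5FU evidence in BACKGROUND concerns anal, rectal, pancreatic, esophageal, head and neck, and cervical cancer, with survival or disease management as the outcome. It contains no bone-pain response rate.
- Expected superiority over 5FU: it rests on pharmacology and a xenograft report, not on a clinical comparison.

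**2. What can one arm estimate?** The hypothesis concerns D = p(capecitabine) - p(5FU). The trial estimates only the first term. Suppose, as an assumption, that 30% respond completely:
- assumed p(5FU) = 20%: D = 30 - 20 = +10 points;
- assumed p(5FU) = 50%: D = 30 - 50 = -20 points.

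Not even the sign is fixed by the data, and more patients would not change this. They would only narrow the interval for the first term. Exact (Clopper-Pearson) 95% intervals at assumed sample sizes:

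| Complete responses / patients (assumed) | 95% interval |
|---|---|
| 6/20 | 11.9% to 54.3% |
| 9/30 | 14.7% to 49.4% |
| 15/50 | 17.9% to 44.6% |

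**3. What would a real comparison need?** For scale only: two-sided alpha 0.05, power 0.80, equal allocation, pooled-variance formula without continuity correction, and an assumed 5FU complete response rate of 20% to 50%. A randomised comparison would need about 294 to 388 patients per arm for a 10-point gain, 138 to 173 for 15 points and 82 to 97 for 20 points.

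**4. Can the response be divided?** The observed response may contain a radiotherapy effect, a systemic capecitabine effect and a sensitization effect. One observed rate cannot separate the three. A radiation-alone rate would remove only the first, and the other two would remain mixed.

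BACKGROUND shows that the first component can be large. In the large RTOG trial of radiotherapy schedules, 89% of patients had at least minimal relief, and breast and prostate primaries were significantly more likely to respond than lung or other primaries. That figure is not a complete response rate, and BACKGROUND gives no complete response rate for 30 Gy in 10 fractions.

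**5. Does item 5 settle the timing?** Its wording most naturally describes patients already on capecitabine, whereas CHEMOTHERAPY describes giving the drug alongside radiotherapy. The text does not say whether patients who begin it with radiotherapy also qualify. The difference matters: baseline pain in an established user is already measured on the drug, whereas in a new starter the systemic effect begins together with radiotherapy.

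**The case against.** The strongest reply is that no comparison is planned. The hypothesis says what capecitabine ought to do, the objectives are descriptive, the study is a pilot, and no test, margin or decision uses a 5FU rate. Deleting the clause would change no procedure. This stands, and it limits the point to what is claimed and concluded. It does not remove the point, because this is the only hypothesis stated and the design cannot answer it.

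A reader might go further and infer that the protocol credits any systemic effect to sensitization. It does not: the primary objective refers outcome to the regimen. What can be said is that the data could not support such a credit.

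A reader might also see a contradiction in the dose. BACKGROUND describes the dose-response evidence as "suggesting that further gains can be realized at doses outside of the range tested", while the trial's schedule lies inside the tested range. The documents do not support that reading. BACKGROUND proposes to raise the biologically effective dose with a sensitizer instead of raising the physical dose, and it never says that this regimen will pass the top of the range. Nor can one state how much enhancement that would take without choosing a radiobiological model, which the protocol does not supply.

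Finally, a radiation-alone reference lacks a figure in the protocol just as 5FU does, and it would not isolate sensitization. That is correct. Such a rate can serve only as context and would have to be sourced. A start-date table may also look like a matter for the analysis plan. The table could be placed there, but the date has to be collected during the trial.

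**Conclusion.** The point holds as a mismatch between the stated hypothesis on one side and the design and objectives on the other. The trial yields no information on superiority over 5FU at any sample size, and it cannot attribute response to sensitization as distinct from radiotherapy or systemic capecitabine. It can estimate the complete response rate of the combined regimen.

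The correction should be made, but it does not threaten the conduct of the study: no formal test depends on the hypothesis, and no calculation is wrong.

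The conclusion rests on two readings of the text: that uniform treatment with no described control means a single arm, and that item 5, an incomplete sentence in the inclusion list, is a requirement. The response rates and sample sizes in the working are assumptions used to show scale, and the conclusion does not depend on them.

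**What to change.** 1. In OBJECTIVES, replace the hypothesis by an estimation aim: the complete response rate, as defined under Assessment of Response, for 30 Gy in 10 fractions given with capecitabine, reported with an exact 95% confidence interval.
2. State that no superiority over 5FU and no proof of sensitization will be claimed, and that conclusions refer to the combined regimen.
3. Clarify in item 5 whether patients must already be on capecitabine or may begin it with radiotherapy. Record the start date and describe response in the two groups separately if both are enrolled.
4. If a radiation-alone rate is shown, give its source and label it as context only.

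The cost is a few sentences, one data field and one descriptive table, which will be small and imprecise and should carry no test. Treatment does not change. Keeping the 5FU claim would require a 5FU comparator, or at the least a justified 5FU reference rate for bone pain. The per-arm numbers in the working suggest that a randomised comparison would be a different study from this pilot.

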**Eligibility Criteria**

Patients with metastatic breast will be allowed on the study regardless of their prior exposure to chemotherapy. Today, there is no evidence to suggest crossresistance between radiotherapy and prior chemotherapy, or that response to radiotherapy is related in any way to the number of lines of chemotherapy used in a particular patient. Good palliative responses can often be achieved in heavily pretreated patients.

1.The patient must be 18 years of age or older.

2.The patient must have histologically proven breast adenocarcinoma.

3. Radiographic evidence of bone metastasis is required .Acceptable studies include plain radiographs, radionuclide bone scans, computed tomography scans and magnetic resonance imaging.

4 .The patient must have pain that appears to be related to the radiographically documented metastasis.

5. Patients receiving systemic therapy with Capecitabine to metastatic disease (according to health basket ).

6. Patients must have an estimated life expectancy of 3 months or greater.

7. Patients will be eligible for treatment of multiple metastases only if these can be included in no more than two treatment sites.

8. Signed study‑specific informed consent.

9 Karnofsky Performance Status > 40.

10**.** Calculated Creatinine Clearance > 50 ml/min

11.ALT and AST no greater than 3‑5 times the institutional normal; bilirubin and serum creatinine no greater than 1.5 times normal; ANC greater than 1500, and platelets at least 100,00.

Exclusion Criteria

1. Prior radiation therapy or prior palliative surgery to the painful site.

2. Impending fracture of the treatment site or planned surgical fixation of the bone.

3. Patients with clinical or radiographic evidence of spinal cord or cauda equina compression.

4. Patients receiving systemic radionuclides (strontium, samarium, etc.) within 60 days prior to registration.

